### Diagnostic work-up for HCC confirmation

If HCC is suspected on liver US or non-contrast liver MRI, a dynamic liver CT with 4 phases will be performed for confirmation. Imaging criteria of arterial hypervascularity and venous or delayed phase washout will be relied on to reach a diagnosis of HCC on dynamic liver CT [9]. If patients are diagnosed with HCC on dynamic liver CT, participation in the clinical trial will be terminated, and the patient will be immediately referred for treatment. If there is no evidence of HCC on dynamic liver CT, the patient will return to the regular surveillance schedule as outlined. If indeterminate lesions are identified on dynamic liver CT, liver MRI or biopsy will be considered. After the last surveillance round, patients with no suspicion of HCC or who have not been diagnosed with HCC during the 3-year follow-up period will be evaluated with a dynamic liver CT to exclude false-negative findings.

### Screening failure and drop-out criteria

Patients who have withdrawn their informed consent prior to the first examination will be regarded as a screening failure. If patients do not receive the next test within one month before or after the appropriate interval from the previous test date, they will be disqualified and labeled dropouts.

### Endpoints

Primary endpoint: comparison of the HCC detection rate by US performed at 6-month intervals with that of yearly non-contrast liver MRI during a 3-year follow-up.

Secondary endpoint: survival of the patients who developed HCC during the 3-year follow-up period.

### Data collection

Data will be collected using electronic case report form (eCRF) (cc.mediex.co.kr). Investigators or designated qualified staff in each institution will enter patient data obtained from US, MRI and laboratory tests during surveillance into eCRF. A valid username and password are needed to log into the eCRF system to secure patient data. Each patient is automatically assigned a unique identification (ID) number at the time of enrollment according to the institution and registration order.

### Statistical analysis

The sensitivity, specificity, positive predictive value, and negative predictive value of liver US and non-contrast liver MRI for the detection of HCC will be determined and compared. Detection rates and false referral rates will be evaluated. The difference in the detection rate of each modality will be compared using the McNemar test. A survival analysis of the patients who develop HCC during the study period will be determined according to the Kaplan-Meier method. A comparison of the survival curves will be made by means of the log-rank test. For continuous variables among clinical and demographic data, the mean, standard deviation, median, minimum, and maximum values will be presented. For comparison between patients with HCC or those without HCC during the study period, Student’s t-test will be used for continuous variables with a normal distribution, and Wilcoxon rank-sum test will be used for those with a non-normal distribution. A chi-square test will be used for categorical variables. Statistical analyses will be performed using SPSS, version 21.0 (IBM, New York, NY). *P-*value ≤0.05 will be considered indicative of a statistically significant difference.

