#### Sample size calculation

To calculate the number of subjects required to achieve statistical significance, the following assumptions were made:A crossover design study was planned for the two groups between US and non-contrast liver MRI.The incidence of cumulative hepatocellular carcinoma was assumed to be 15% for 3 years (5% per year) [28].The sensitivity of non-contrast liver MRI was assumed to be 80%, and the sensitivity of US was assumed to be 60% [27, 29].Type I error (α) = 5% and the power (1-β) = 80% were assumed.

A sample size of 192 patients was calculated to achieve 80% power for a difference in HCC detection of 60% for US and 80% for non-contrast liver MRI. The required sample size was 211 patients, assuming a drop-out rate of approximately 10%.

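### Student's t-test, conditioned on normality alone, will not hold its 5% level in an HCC versus no-HCC split of about 29 to 163 if the spreads differ; Welch's test would, and no endpoint is affected

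*Protocol article*

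**What the plan says.** In the protocol article, the Statistical analysis section sets a two-way rule for comparing continuous variables between patients with and without HCC. Student's "t-test will be used for continuous variables with a normal distribution", and the "Wilcoxon rank-sum test will be used for those with a non-normal distribution". The sentence just before it, which sets out the descriptive summaries, opens with "For continuous variables among clinical and demographic data", so these are the variables concerned. The section's threshold is that a P-"value ≤0.05 will be considered indicative of a statistically significant difference". Equal variance is not mentioned, either as an assumption or as something to be checked.

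The expected group sizes follow from the Sample size calculation section: "The incidence of cumulative hepatocellular carcinoma was assumed to be 15% for 3 years (5% per year", and "A sample size of 192 patients was calculated to achieve 80% power".

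The same Statistical analysis section gives the primary comparison of detection rates to the McNemar test, and survival to Kaplan-Meier curves and the log-rank test.

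**The concern.** Student's t-test in strict usage estimates one common variance from both groups together. When the groups are of similar size, unequal variances do little harm. When one group is more than five times the other, the common variance is essentially that of the large group, while the uncertainty in the mean difference comes mostly from the small group. If the HCC group is the more variable, the standard error is too small and P-values are too low. If it is the less variable, the reverse holds.

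Nothing in the design guarantees equal spread. The groups are not randomised; they are formed by who develops HCC, so equal means for a variable would not imply equal SDs. A rule that sends variables to the t-test on normality alone passes over the assumption that matters more with this imbalance.

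At stake is whether HCC and no-HCC patients are reported as differing on a clinical or demographic variable at an error rate other than the 5% that the plan states.

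**Working it through.** **Inputs from the document.** 192 evaluable patients, 15% cumulative HCC incidence and the 60% v 80% sensitivities (Sample size calculation); Student's t-test and a 0.05 threshold (Statistical analysis), taken here as two-sided because sidedness is not stated.

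**Input that is assumed.** The SD ratio r = SD(HCC) / SD(no HCC). The document gives no SDs, so a range of r is shown.

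**1. The plan's own figure.** The 192 can be reproduced with the McNemar formula if every cancer found by ultrasonography is also found by MRI (discordance 0.20, difference 0.20) and α is one-sided 5%:

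(1.645 × √0.20 + 0.842 × √(0.20 − 0.04))² / 0.04 = (0.7356 + 0.3366)² / 0.04 = 28.7 HCC cases; 28.7 / 0.15 = 191.6, rounded to 192.

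Whether those inputs are suitable is a separate matter. What counts here is that the plan's size rests on about 29 HCC cases.

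**2. Group sizes.** 192 × 0.15 = 28.8, about 29 with HCC; 192 − 28.8 = 163.2, about 163 without. The size ratio is 163 / 29 = 5.6.

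**3. Why the pooled test drifts.** Set the no-HCC SD to 1.
- Pooled variance = (28r² + 162) / 190. The HCC group has weight 28/190 = 15% and the no-HCC group 162/190 = 85%.
- Variance that the pooled test uses for the mean difference = pooled variance × (1/29 + 1/163) = pooled variance × 0.0406.
- True variance of the mean difference = r²/29 + 1/163.

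Example, r = 1.5: the pooled variance is (63 + 162) / 190 = 1.184, so the test uses 1.184 × 0.0406 = 0.0481. The true value is 2.25/29 + 1/163 = 0.0837. The standard error is too small by the factor √(0.0481 / 0.0837) = 0.758. The critical value 1.973 (190 degrees of freedom) then acts like 1.973 × 0.758 = 1.495, and a standard normal variable exceeds ±1.495 about 13.5% of the time.

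The same steps give 0.2% at r = 0.5 and 20.9% at r = 2. These are large-sample approximations to the simulation below.

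**4. Simulation.** Normal data, equal means, groups of 29 and 163, two-sided 5%, 400,000 draws per setting:

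| r (HCC / no HCC) | Student (pooled) | Welch |
|---|---|---|
| 0.5 | 0.2% | 5.0% |
| 0.67 | 1.0% | 5.0% |
| 0.8 | 2.2% | 5.0% |
| 1.0 | 5.0% | 5.0% |
| 1.25 | 9.3% | 5.0% |
| 1.5 | 13.6% | 5.0% |
| 2.0 | 21.0% | 5.0% |

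Using the 211 enrolled instead (about 32 v 179) gives practically the same rates, for example 13.6% at r = 1.5 and 21.1% at r = 2.

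**5. Two other routes.** Choosing between Student and Welch by a preliminary test of equal variances (20,000 simulated data sets) gives 3.9% at r = 0.75, 7.2% at 1.33 and 6.4% at 1.5. That is better than pooling but less steady than Welch alone. Sending every variable to the rank-sum test does not cure the problem either: on normal data with equal means it rejects 8.4% of the time at r = 1.5 and 11.4% at r = 2 (5,000 data sets).

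**The case against.** Four points can be made against this, and most of each stands.

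**The range is not a property of the plan.** This is correct. Every figure away from 5% depends on an SD ratio that the document does not give. All patients meet the same cirrhosis, age and risk-index criteria, and nothing suggests that any normally distributed variable has twice the SD in one group. A reader might infer that the error rate will be anywhere from 1% to 21%. The document does not support that: the 1% belongs to a ratio of 0.67 and the 21% to a ratio of 2, so the pair is not even a consistent range. Only ranges tied to matched ratios can be stated.

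**Pooling is an interpretation.** The section names Student's t-test and does not use the word pooled. A condensed article may use the name loosely, and the handling of unequal variances could be settled in a fuller document. This limits the point to what follows if the name means what it strictly means. It does not remove it, because the article states a method and its condition rather than leaving the choice open.

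**No endpoint depends on it.** This is also correct. A reader might infer that the comparison of ultrasonography with MRI, or the survival analysis, is compromised. Neither uses a t-test.

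**Type I error matters only where the means do not differ.** Age, platelet count and prothrombin activity are already in the entry risk index as predictors of HCC, so the plan would expect true differences there. That is fair, and the error rates apply to variables without a true difference in means. For the others, the wrong standard error still distorts P-values, though the 5% benchmark is then not the relevant one.

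**Conclusion.** The point holds as a minor, low-cost improvement. The named test, in its strict sense, holds 5% with groups of about 29 and 163 only if the SDs are about equal, and the plan neither assumes nor checks that. For normal data with equal means, the error rate is:

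- about 2% to 9% for SD ratios 0.8 to 1.25;
- about 1% to 14% for ratios 0.67 to 1.5;
- about 0.2% to 21% for ratios 0.5 to 2.

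The ratios are assumptions; the 29 and 163 come from the plan's own incidence and sample size. Even the mildest band more than halves or nearly doubles the stated level. The effect is confined to supporting comparisons of clinical and demographic variables and changes no conclusion about either endpoint.

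**What to change.** In the Statistical analysis section, name Welch's unequal-variance t-test in place of Student's t-test for normally distributed continuous variables compared between patients with and without HCC. Use it outright, without a preliminary test of equal variances.

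The cost is a change of wording. Data collection, sample size and endpoints stay as they are. Under equal variances nothing is lost in error control, since Welch's test also gives 5.0% at a ratio of 1.

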## Discussion

Disease surveillance tools must be sensitive, cost-effective, and accessible. US is an efficient tool in terms of cost-effectiveness and ease of accessibility. However, US has a number of drawbacks, including limited depth penetration, poor sensitivity for detecting small lesions, and an inability to assess the entire liver [3, 20]. The efficacy of US is also operator-dependent and can be affected by several patient characteristics, such as obesity, a fatty liver, and macronodular cirrhosis [2, 13, 14, 29, 31]. All of these factors impair the sensitivity of US screening for HCC. Nevertheless, US is exclusively used as an imaging tool for HCC surveillance. A new and highly sensitive imaging modality is therefore needed for early detection of HCC in high-risk patients, which will improve survival and prognosis.

We designed a prospective crossover design with a single arm of patients. Of course, a randomized controlled trial (RCT) is the best design for comparing the effectiveness of an intervention. To date, there have been two RCTs evaluating HCC surveillance by US in China [6, 32]. However, these two studies were plagued by serious ethical concerns. There was a lack of information regarding the process of informed consent and the availability of local clinical services. In addition, participants were not offered the options of undergoing nonrandomized screening and declining screening. As a result of these improprieties, regulations surrounding research ethics have been strengthened, and there have been no RCTs evaluating HCC surveillance tools [33]. We believe that this present study design is able to properly assess the efficiency of surveillance tools for HCC.

MRI is the most sensitive modality for the detection of HCC [15]. However, MRI is not commonly used as a screening modality due to the high cost, long examination time, low accessibility and the risk of adverse effect from the contrast media. There is also little evidence supporting the efficacy of MRI for HCC surveillance. In this trial, we modified two factors to counter these objections to using MRI examination as a surveillance tool. First, the MRI will be performed without the use of intravenous contrast. Arterial enhancement after contrast injection is one of the major criteria for diagnosing HCC. However, in reality, intravenous contrast is not necessary in a surveillance step. Rather, it is more important to detect focal hepatic lesions with high sensitivity in high-risk patients. T2WIs have a high sensitivity for detecting focal liver lesions, and DWIs are effective in detecting and characterizing HCC in cirrhotic patients [34, 35], especially small HCC (<2 cm) [36]. In addition, high b-values on DWI offer excellent specificity in distinguishing HCC from benign cirrhotic nodules and pseudo-lesions [37]. If the MRI examination is performed using these basic sequences without contrast, this method is quite adequate for HCC surveillance. The study also takes only 10–15 min, which is less time than when contrast-enhanced dynamic images are obtained.

In the study protocol, MRIs will be obtained annually and US bi-annually. MRIs will be obtained every 12 months, an acceptable interval range for HCC surveillance based on the recommendation to obtain imaging studies every 6 to 12 months [15]. Thus, the high cost of MRI will be offset by fewer examinations. In addition, the increased time interval between studies will be offset by the superior sensitivity of MRI for HCC detection. In summary, fewer studies compensated by superior sensitivity can decrease the overall cost of MRI and increase its appeal as a screening tool.

This is the first study to evaluate the feasibility of non-contrast MRI compared with US as a surveillance tool for detecting HCC in high-risk patients. We expect that the results support the efficacy of non-contrast MRI as a screening tool for HCC in this patient population.

## Abbreviations

ADC: Afferent diffusion coefficient
AFP: α-fetoprotein
DWI: Diffusion-weighted image
FSE: Fast spin echo
GRE: gradient echo
HBsAg: Hepatitis B virus surface antigen
HCC: Hepatocellular carcinoma
HCV-Ab: Hepatitis C virus antibody
MRI: Magnetic resonance imaging
PIVKA-II: Vitamin K absence/antagonist II
T1WI: T1-weighted image
T2WI: T2-weighted image
US: Ultrasonography
